**Methods:**

This single-center, randomized, sham-controlled pilot trial will enroll 60 T2DM patients with metformin-associated GI AEs, randomized 1:1 to either the taVNS group or the sham control group. The intervention lasts 2 weeks with a follow-up at week 4. Assessments at baseline and follow-up include a validated Metformin Symptom Severity Score (total score 0–50; primary outcome), Bristol Stool Form Scale, bowel urgency, glycaemic/metabolic indices [fasting blood glucose (FBG), 2-h postprandial glucose (PG2h), glycated albumin (GA), fasting C-peptide, fasting insulin, HOMA-IR, ISI], and mechanistic biomarkers (GLP-1, 5-HT, IL-6, IL-10, TNF-α, D-lactate, DAO, bile acids). Safety monitoring includes routine hematology, liver and renal function tests.

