Because adherence is inversely associated with glycaemic control and directly associated with reduced healthcare costs (Lawerence et al., 2006), sustained metformin use is critical for disease management. Given the dose-dependent nature of metformin's efficacy [with optimal glycaemic effects observed near 2,000 mg/day (Garber et al., 1997)], attenuating GI AEs without reducing dose has important implications for treatment outcomes. Current clinical management largely relies on dose adjustment or adjunctive symptomatic therapies and lacks a systematic, mechanism-based “enhance-efficacy/reduce-toxicity” strategy rooted in the gut–brain–metabolic axis.

Against this pathophysiological background, non-invasive vagal modulation via transcutaneous auricular vagus nerve stimulation (taVNS) offers a novel therapeutic perspective. taVNS selectively activates the auricular branch of the vagus nerve (ABVN) and, through an ear–vagus–brainstem–gut circuit (Zou et al., 2026), can modulate central-peripheral autonomic balance, engage cholinergic anti-inflammatory pathways, regulate gut motility, influence endocrine mediators (including GLP-1 and 5-HT), and affect bile-acid metabolism, while indirectly reshaping the gut microbiota and barrier function (The Wingate Institute of Neurogastroenterology TBI, 2020; Seitz et al., 2022; Zhao et al., 2025; Zhang et al., 2025; Zou et al., 2024). Thus, taVNS could theoretically mitigate local inflammation and functional perturbations induced by metformin without necessitating dose reduction, thereby improving tolerability and synergistically enhancing metabolic control. The ear concha region corresponds anatomically to a dense distribution of ABVN fibers (The Wingate Institute of Neurogastroenterology TBI, 2020); transcutaneous stimulation of this area activates vagal pathways while avoiding the invasiveness of implanted VNS and can influence both gastrointestinal function and glucose metabolism (Zou et al., 2024; He et al., 2013).

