#### Diagnostic criteria for metformin intolerance

2.3.2

Metformin intolerance will be defined as meeting any of the following criteria (McCreight et al., 2018):

(1) Prior use of metformin with treatment discontinuation due to gastrointestinal intolerance (prior exposure ≤ 1,000 mg/day for ≤ 8 weeks); or(2) Inadequate glycaemic control [e.g., HbA1c ≥ 7.0% (53 mmol/mol)] with inability to escalate metformin to ≥500 mg/day because of intolerable gastrointestinal symptoms.

(Reference tolerability: individuals taking divided doses of metformin up to 2,000 mg/day without clinically significant gastrointestinal adverse effects.) Other causes of diarrhea must be excluded before confirming the diagnosis (McCreight et al., 2018).

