#### Inclusion criteria

2.3.3

Participants must meet all of the following:

(1) Fulfill the diagnostic criteria for T2DM and for metformin intolerance as defined above;(2) Aged 18–80 years (inclusive), any sex;(3) Able and willing to comply with study procedures and to provide written informed consent;(4) Stable diet, exercise, lifestyle and antihyperglycaemic regimen, with a fasting blood glucose coefficient of variation (CV) < 16% during the 3 days preceding baseline and on the day of enrollment;(5) Body mass index (BMI) between 18.5 and 40.0 kg/m^2^.

Only participants who satisfy all five criteria will be enrolled.

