##### Bowel urgency

2.7.3.2

Bowel urgency reflects the temporal urgency for defecation following medication. The shortest daily response interval is recorded and quantified on a 0–3 scale: 0 = no urge/>3 h, 1 = ≤ 3 h, 2 = ≤ 2 h, 3 = ≤ 1 h. Assessment time points are baseline, Week 2, and Week 4.

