Mechanistically, the effects of taVNS extend beyond peripheral modulation of gastrointestinal nerves. It likely activates central vagal circuits, including the nucleus tractus solitarius (NTS), dorsal motor nucleus of the vagus (DMV), and locus coeruleus, thereby influencing thalamo–hypothalamic integrative networks and coordinating gastrointestinal motility, mucosal barrier integrity, and metabolic signaling (He et al., 2013). Previous studies have demonstrated that taVNS promotes endogenous acetylcholine release, activates cholinergic anti-inflammatory pathways, and improves the gastrointestinal mucosal microenvironment, mitigating drug-induced intestinal hyperreactivity. taVNS may rebalance autonomic tone, with the potential to ameliorate metformin-induced gastric emptying delay and dysmotility, and stabilize pharmacokinetics, allowing patients to maintain glycemic control without dose reduction (The Wingate Institute of Neurogastroenterology TBI, 2020). This would create a novel balance between detoxification and potentiation, providing a feasible neuromodulatory strategy for comprehensive T2DM management.

Although this clinical study will focus on gastrointestinal symptoms and glycemic outcomes, the systemic effects of taVNS likely involve broader molecular and metabolic pathways. Vagal modulation is closely linked with gut microbiota homeostasis, affecting short-chain fatty acid and bile acid metabolism and intestinal barrier integrity, which may indirectly influence drug response and metabolic regulation (Zhang et al., 2025). Confirmation of these effects would provide mechanistic depth to our clinical findings and establish a basis for a multilevel central–peripheral–microecological regulatory model.

From a translational perspective, this study expands the application of taVNS to drug-related gastrointestinal intolerance, distinguishing it from prior research that primarily focused on postoperative nausea or functional dyspepsia. If the findings support our hypothesis, it would demonstrate the multidimensional potential of taVNS in modulating adverse drug reactions. Furthermore, if these findings are replicated in future multicenter trials, taVNS may become a feasible adjunctive strategy for T2DM management, particularly during high-dose metformin therapy, offering a non-pharmacological, low-side-effect approach to optimize tolerability.

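### As written, the entry criteria do not select patients with current metformin-associated GI symptoms, the population that the abstract and the aim name

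*Protocol article*

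**What the plan says.** The abstract states that the trial "will enroll 60 T2DM patients with metformin-associated GI AEs", and section 2.1 gives the aim as alleviating those events. The Introduction sets the motive: "attenuating GI AEs without reducing dose has important implications for treatment outcomes".

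Eligibility is fixed in two places. Section 2.3.3, criterion 1, requires participants to "Fulfill the diagnostic criteria for T2DM and for metformin intolerance as defined above". Section 2.3.2 supplies the definition: "Metformin intolerance will be defined as meeting any of the following criteria".

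- Route 1: "Prior use of metformin with treatment discontinuation due to gastrointestinal intolerance (prior exposure ≤ 1,000 mg/day for ≤ 8 weeks".
- Route 2: inadequate glycaemic control together with "inability to escalate metformin to ≥500 mg/day because of intolerable gastrointestinal symptoms".

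The other four inclusion criteria cover age, consent and compliance, a stable regimen with limited glucose variability, and BMI. Section 2.7.2 says that the symptom questionnaire is not a basis for diagnosis. Section 2.6.1 gives all participants metformin as background therapy, started at 500 mg twice daily and titrated weekly.

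**The concern.** Relieving symptoms that a patient now has, and keeping symptoms from returning when a patient takes the drug again, are different questions. They have different baselines and different expected courses in the sham group. The abstract and aim state the first question. The criteria let in people for whom only the second can be asked, and they turn away one group for whom the first is most natural.

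This matters for a pilot. Section 2.4 makes the SD of the primary score the core output for a later definitive trial. A reader of that SD, or of any effect estimate, needs to know which patients and which question it describes. The analysis as specified does not separate the two kinds of entrant.

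**Working it through.** No sample-size figure is in dispute. The plan's own numbers reproduce: 25 / 0.85 = 29.4, rounded up to 30 per group and 60 in total; 2 × 25 − 2 = 48 degrees of freedom. The check is to apply the criteria to each type of patient.

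1. **Takes 500 mg/day or more, has GI symptoms now, never stopped.** Route 1 fails because there was no discontinuation. Route 2 fails because 500 mg/day was reached. Not eligible.
2. **Takes less than 500 mg/day, has symptoms, adequate control, never stopped.** Route 1 fails; route 2 fails on glycaemic control. Not eligible.
3. **Stopped earlier because of GI effects, off the drug, no symptoms today.** Route 1 is met. The 8-week limit there concerns the length of the earlier exposure, not how long ago it ended. Eligible.
4. **Could not reach 500 mg/day, inadequate control.** Route 2 is met, with or without symptoms at the present dose. Eligible.
5. **Stopped once, restarted, has symptoms now.** Route 1 is met through the earlier discontinuation. Eligible.

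The exclusion criteria in 2.3.4 do not change this classification, since none concerns absence of symptoms or of current metformin use. No run-in on metformin and no symptom check before baseline is described.

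**What the baseline measures in type 3.** Items 6 to 8 in Table 2 each carry 1 point for presence, up to 4 for frequency and up to 5 for severity: 1 + 4 + 5 = 10, so 3 × 10 = 30 points. Their recall period is the final week on metformin, not the week before the visit. For someone off the drug, that week lies at an unstated distance in the past. At Weeks 2 and 4, once metformin has been restarted, the same items refer to the present treatment. Baseline and follow-up then describe two different episodes of exposure.

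**What the analysis does with it.** Randomisation is stratified by age and gender (2.5). The mixed model in 2.10 has group, time and their interaction as fixed effects. Baseline metformin dose appears only in the imputation model. Status at entry is nonetheless collected: Table 2 item 1 asks whether the patient still takes metformin, and 2.7.1 records the current glucose-lowering regimen.

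**Passages that do not fit together.** Route 2 describes patients who could not reach 500 mg/day. Section 2.6.1 starts everyone at 2 × 500 = 1,000 mg/day. Section 2.3.3, criterion 4, asks for a stable antihyperglycaemic regimen at entry. These must be reconciled with each other and with the stated aim. No view is taken here on which dose or rule is right.

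**The case against.** The best defence is that the protocol also states its target as intolerance. The abstract's discussion and section 3 speak of metformin-associated GI intolerance, and 2.1 of improving drug tolerance. People who gave up metformin because of GI effects are central to that problem. Route 2 requires intolerable GI symptoms on escalation, so its entrants are intolerant by definition even if comfortable at their present dose. Stimulating intolerant patients while metformin is given is a coherent design. All of this stands. It shows that re-exposure is a legitimate question, but not that it is the one the abstract and aim state.

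A reader might infer several stronger points that the documents do not support:

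- *Many participants have nothing to relieve.* The split between routes is not given. The baseline score is not empty either: a former user who stopped at 1,000 mg/day or less carries 5 + 5 + (2 to 4) + (0 to 2) + (0 to 2) = 12 to 18 points from items 1 to 5 alone.
- *All symptomatic patients on 500 mg/day or more are shut out.* Type 5 above can enter.
- *The trial yields no data at higher doses*, although the discussion looks to use "particularly during high-dose metformin therapy". Entry dose is not on-treatment dose; 2.6.1 titrates up to 2,000 mg/day or the maximal tolerated dose.
- *Baseline urgency is zero by construction off the drug.* Section 2.7.3.2 says "Bowel urgency reflects the temporal urgency for defecation following medication", without naming metformin or giving a rule for people not taking it.
- *The SD is inflated.* Nothing in the documents gives the direction or size of any effect, and an SD from this sample would carry over to a later trial with the same criteria.

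Finally, 2.6.1 does not date the metformin start against the 1-week baseline period in 2.6.5. A start before Day 0 would give some on-drug baseline, but the text does not say so.

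**Conclusion.** The point holds in a limited form. The criteria and the stated population disagree. Current use and current symptoms are not required, symptom-free former users qualify without a recency limit, and never-stopped patients with symptoms on 500 mg/day or more do not qualify. For entrants off the drug, the symptom part of the primary baseline is undated recall, and the question answered is tolerance on re-exposure.

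The size cannot be stated. The criteria put no bound on the share of off-drug entrants, so it could lie anywhere from none to all 60. The conclusion rests on a literal reading of 2.3.2 and 2.3.3 and on there being no on-drug run-in before Day 0. The enrolment target and the 48 degrees of freedom are unaffected.

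**What to change.** Reconcile the abstract, 2.1, 2.3.2, 2.3.3 (criterion 4) and 2.6.1 in one of two ways:

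- (a) admit current metformin users with at least one Table 2 symptom (items 6 to 8) in the 7 days before baseline; or
- (b) restate the objective as improving tolerance on metformin re-exposure, and give route 1 a recency limit.

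In either case, add on/off-metformin status at entry as a covariate in the linear mixed model of 2.10, and describe the primary score by that status. The data are already collected. No dose is proposed.

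A further randomisation stratum is not needed in 60 people. Nor are separate SD estimates as a formal output. With 50 evaluable in two arms, an assumed 30% off the drug would give 15 people and 15 − 2 = 13 degrees of freedom, under the protocol's own threshold of 20. Both subsets reach 20 only if 22 to 28 of the 50 enter off the drug.

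The cost is an amendment to the eligibility or the objective text, and one model term.

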#### Inclusion criteria

2.3.3

Participants must meet all of the following:

(1) Fulfill the diagnostic criteria for T2DM and for metformin intolerance as defined above;(2) Aged 18–80 years (inclusive), any sex;(3) Able and willing to comply with study procedures and to provide written informed consent;(4) Stable diet, exercise, lifestyle and antihyperglycaemic regimen, with a fasting blood glucose coefficient of variation (CV) < 16% during the 3 days preceding baseline and on the day of enrollment;(5) Body mass index (BMI) between 18.5 and 40.0 kg/m^2^.

Only participants who satisfy all five criteria will be enrolled.

#### Exclusion criteria

2.3.4

Subjects meeting any of the following will be excluded:

(1) Acute or chronic diarrhea attributable to confirmed gastrointestinal pathology or systemic disease (including but not limited to hepatic, biliary or pancreatic disease; infectious diarrhoeal illnesses such as dysentery or cholera; systemic diseases, intoxications, parasitic infections; malignancy; prior gastric bypass surgery);(2) Severe cardiovascular or cerebrovascular disease, diabetic ketoacidosis, or other serious endocrine, haematologic or psychiatric disorders likely to affect compliance or follow-up;(3) Use of antibiotics, proton pump inhibitors, H_2_-receptor antagonists, probiotics/prebiotics or other agents known to substantially alter the gut microbiota within 4 weeks prior to enrollment;(4) Pregnancy, planned pregnancy, or lactation;(5) Marked glycaemic instability;(6) Current insulin therapy;(7) Severe skin lesions in the auricular concha or absence/deformity of the auricle that precludes intervention;(8) Fear of the intervention or inability to tolerate conventional electrical stimulation;(9) Known allergy or contraindication to metformin hydrochloride;(10) Participation in another clinical trial or any condition likely to prevent completion of the study follow-up.

Note: any participant who meets one or more of the exclusion criteria above will be ineligible for enrollment.

### Sample size justification

2.4

Sample size for this randomized, sham-controlled pilot and feasibility trial was determined in full alignment with the CONSORT 2010 Statement: Extension to Randomized Pilot and Feasibility Trials (Eldridge et al., 2016), and the optimized sample size estimation method for pilot trials with continuous primary outcomes established by Whitehead et al (Whitehead et al., 2016). As an external pilot trial, the core aim of sample size setting is not to power formal hypothesis testing for intervention efficacy, but to generate a sufficiently precise estimate of the standard deviation of our primary outcome (Metformin Symptom Severity Score total score) to inform the design of a future definitive randomized controlled trial. In detail, according to the optimized sample size estimation method for pilot trials established by Whitehead et al., an estimated final sample of 25 evaluable participants per group (after accounting for a 15% attrition rate from the 30 enrolled participants) yields 48 degrees of freedom for variance estimation. This well exceeds the minimum threshold of 20 degrees of freedom recommended in the literature for stable, unbiased variance estimation in pilot research. No formal hypothesis testing for intervention efficacy is planned in this pilot trial. Core feasibility endpoints include: recruitment rate (target ≥8 participants per month), screening failure rate, treatment adherence rate (defined as completing ≥80% of scheduled treatment sessions), attrition rate (estimated at 15% based on published neuromodulation trials in patients with T2DM), and protocol violation rate. Accounting for a 15% attrition rate, the final enrollment target is 60 participants (30 per group) (Whitehead et al., 2016).

### Randomization and blinding

2.5

Participants will be randomized 1:1 to taVNS group or sham control group, with stratification by age and gender to balance baseline characteristics between groups. The randomization sequence will be generated by an independent third-party biostatistician using SPSS 26.0, with group allocation sealed in sequentially numbered, opaque envelopes for strict allocation concealment. After baseline assessment, a dedicated study coordinator (fully blinded to group assignment) will open envelopes in numerical order to assign eligible participants.

Given the anatomical specificity of active and sham stimulation sites, intervention staff responsible for electrode placement and device operation cannot be blinded to group allocation. To mitigate potential bias, we have implemented pre-specified rigorous safeguards: The blinded coordinator exclusively manages group allocation, and only provides intervention staff with pre-marked anatomical diagrams of stimulation sites, with no disclosure of group identity at any time. Non-blinded intervention staff are strictly barred from outcome assessment, data entry, statistical analysis, or any communication with participants about group allocation or expected intervention effects. Both groups use identical stimulators with consistent nominal parameters; all intervention staff receive centralized standardized training to ensure identical operational execution and participant interaction across groups.

All outcome assessors, data analysts, biostatisticians, and participants will remain fully blinded to group allocation throughout the trial. Furthermore, treating physicians are solely responsible for routine clinical management and safety assessments; they have no access to group allocation and are strictly isolated from intervention implementation and outcome assessment. Participants will be informed that both interventions may induce a mild tingling sensation, and subjective feeling cannot be used to infer group assignment, to minimize anticipation bias. Outcome assessors will receive standardized training and regular inter-rater reliability checks to reduce measurement bias.

The effectiveness of the blinding will be formally assessed in Weeks 2 and 4 using the validated James Blinding Index (BI) method (James et al., 1996). The detailed statistical procedures for this assessment are outlined in the “Statistical Methods” section.

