#### Primary efficacy outcome and assessment time points

2.7.2

The primary efficacy endpoint is the total score of the Metformin Symptom Severity Score, a validated, widely used self-report tool originally developed and psychometrically validated by McCreight et al. specifically for evaluating metformin-related gastrointestinal intolerance in adults with T2DM (McCreight et al., 2018).

In the original validation study by McCreight et al., this questionnaire demonstrated excellent reliability and validity: it showed strong internal consistency (Cronbach's α > 0.8), good test-retest reliability, and significant discriminant validity, with a highly significant difference in total scores between metformin-intolerant and metformin-tolerant patients (*P* < 0.0001) (McCreight et al., 2018). The questionnaire covers medication adherence, reasons for discontinuation, dose tolerance, gastrointestinal symptoms (nausea, abdominal bloating/pain, and diarrhea; frequency and subjective severity), changes in baseline symptoms, and an overall subjective tolerance rating, with a total score ranging from 0 to 50 points (0–10 = tolerable, 11–20 = mild intolerance, 21–30 = intolerable, 31–50 = severe intolerance). This questionnaire is used for the quantitative assessment of intolerance-related symptoms in this trial, not as a basis for clinical diagnosis.

Assessment time points include baseline, Week 2, and Week 4. Details of the questionnaire items and scoring criteria are provided in Table 2 (McCreight et al., 2018).

**Table 2 T2:** The metformin symptom severity score questionnaire.

No	Question	Option	Score
1	Are you still taking metformin?	Yes (skip to question 6)	0
		No	5
2	If you have stopped taking metformin, was it due to side effects?	Yes (continue to question 3)	5
		No (skip to question 6)	0
3	What dose were you taking at the time of discontinuing metformin?	500 mg once daily (1 tablet)	4
		1,000 mg once daily (2 tablets)	3
		500 mg twice daily (2 tablets)	2
		2,000 mg once daily (4 tablets)	1
		1,000 mg twice daily (2 tablets)	0
4	Have you ever taken a lower dose of metformin and tolerated it well?	Yes	0
		No	1
	If yes, what was the maximum dose you tolerated?	(e.g., 500 mg once daily)	2
5	Have you been trialed on a modified release preparation of metformin (e.g. Glucophage SR)?	Yes	2
		No	0
In the last week of taking metformin, have you experienced?			
6	Nausea?	Yes	1
		No	0
	If yes, how often?	More than once a day	4
		Once a day	3
		Occasionally	2

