### Statistical methods

2.10

All data will be managed according to GCP guidelines for clinical trials. Two independent researchers will perform double data entry for all variables, including bowel urgency scores, glucose and insulin metabolism markers, serum inflammatory markers, and safety parameters. Cross-verification is mandatory, and the database will be locked without authorization.

Statistical analyses will be performed by blinded biostatisticians using SAS 9.4 and R 4.2.1. Two analysis sets will be applied: the intention-to-treat (ITT) set includes all randomized participants, and the per-protocol (PP) set includes participants completing ≥80% of the treatment course without major protocol violations, for sensitivity analysis.

Baseline characteristics will be summarized by group. Continuous variables are assessed for normality using the Shapiro–Wilk test: normally distributed variables are presented as mean ± SD, non-normal as median [IQR]; variance homogeneity is assessed via Levene's test. Categorical variables are expressed as counts (*n*) and percentages (%). Between-group comparisons: independent *t*-test or Mann–Whitney *U*-test for continuous variables, Pearson χ^2^ or Fisher's exact test for categorical variables.

Primary and continuous outcome variables (bowel urgency score, FBG, PG2h, FINS, C-peptide, HOMA-IR, ISI, GA, serum IL-6/IL-10/TNF-α, GLP-1, 5-HT, D-lactate, diamine oxidase, and fecal bile acids) will be analyzed using linear mixed-effects models (fixed effects: group, time, interaction; random effect: participant), reporting least-squares means with 95% *CI*. The exact mathematical formulas and covariance structures for these linear mixed-effects models will be fully reported in the final trial publication. Categorical outcomes are analyzed via χ^2^ or Fisher's exact test.

A Multiple Imputation (MI) model will be used as the primary method for missing data. The imputation model will include all primary and secondary outcomes, plus baseline covariates (age, sex, duration of diabetes, baseline metformin dose, baseline Metformin Symptom Severity Score score), with 20 Markov Chain Monte Carlo iterations to generate 20 imputed datasets. The pre-specified linear mixed-effects model will be performed on each dataset, with results pooled via Rubin's rules (Heymans and Twisk, 2022).

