Complete case analysis will be conducted as a sensitivity analysis to verify the robustness of the core findings. Exploratory subgroup analyses stratified by age, sex, and diabetes duration are descriptive only.

The success of blinding will be evaluated using the James BI for all participants and independent outcome assessors at Week 2 and Week 4. The BI is scaled from 0 (all participants guessed correctly) to 1 (all participants guessed incorrectly), with 0.5 indicating completely random guesses (the standard for successful blinding). Weights are assigned consistent with the original James method: 0.00 for correct guesses, 1.00 for incorrect guesses, and 0.50 for uncertain/unable to judge responses, with uncertain responses split equally between correct and incorrect guesses. The BI and its 95% CI will be calculated using the jack-knife procedure recommended in the original method (James et al., 1996).

Safety parameters (CBC, ALT, AST, urea, creatinine) are analyzed similarly, comparing abnormality rates. All tests are two-sided with α = 0.05; effect sizes are reported with 95% CI.

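### The section 2.10 mixed model has no term for whether a participant is taking metformin at entry, a status worth 12 to 18 points on the baseline primary score

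*Protocol article*

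**What the plan says.** **Randomisation (section 2.5).** Allocation is 1:1, "with stratification by age and gender to balance baseline characteristics between groups". Metformin status is not a stratum.

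**Who can enter (section 2.3.2).** Either of two criteria is enough. Criterion (1) is "Prior use of metformin with treatment discontinuation due to gastrointestinal intolerance", with earlier exposure of no more than 1,000 mg/day. Criterion (2) covers poorly controlled people who cannot escalate the drug, and they may still be taking it.

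**How the primary score treats the two states (section 2.7.2, Table 2).** Item 1 gives 0 to a person still taking metformin and sends them straight to item 6. A person who has stopped gets 5 and goes on to item 2, "If you have stopped taking metformin, was it due to side effects", which adds 5 for yes. Items 3 to 5 then add points for the dose at stopping, tolerance of a lower dose, and a trial of modified release.

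**Treatment during the trial (section 2.6).** Metformin is background therapy in both arms.

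**Analysis (section 2.10).** The mixed model has group, time and their interaction as fixed effects and participant as random effect. Baseline dose and baseline score are named for the imputation model: "baseline covariates (age, sex, duration of diabetes, baseline metformin dose, baseline Metformin Symptom Severity Score score". On subgroups: "Exploratory subgroup analyses stratified by age, sex, and diabetes duration are descriptive only".

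**General assessments (section 2.7.1).** The current glucose-lowering regimen is among the baseline data, and the section says these data will serve confounder adjustment and subgroup work.

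**The concern.** Items 1 to 5 place a block of points on the baseline score that depends on whether the person is on the drug that day, not on current symptoms. When metformin is resumed the block drops to zero whatever the stimulation does. A random participant intercept absorbs a difference that is constant over visits. It cannot absorb one that is present at baseline and gone at Week 2.

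Two things are at stake. If the arms differ by chance in the share entering off drug, the group-by-time contrast moves by that difference times the gap. Even with balanced arms, unmodelled status adds variance to the change score and to the baseline score. The pilot is meant to supply effect-size estimates (Abstract, Discussion) and an SD of the total score (section 2.4), so both products would depend partly on the recruitment mix.

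**Working it through.** **1. The plan's own figure.** 30 × 0.85 = 25.5, taken as 25 per arm; 2 × 25 − 2 = 48. This agrees with section 2.4 ("yields 48 degrees of freedom for variance estimation"), and nothing below changes it.

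**2. Baseline gap from items 1 to 5 for someone who stopped for side effects.**
- Item 1: 5. Item 2: 5.
- Item 3: 2 to 4 at 1,000 mg/day or less (0 to 4 over all listed doses).
- Item 4: 0 to 2. Item 5: 0 or 2.
- With the cap of criterion (1): 5 + 5 + (2 to 4) + (0 to 2) + (0 to 2) = 12 to 18.
- Table alone: 10 to 18.
- Still taking metformin: 0.

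**3. Chance imbalance.** The off-drug share p is not given, so it is varied. Off-drug entrants split over 30 and 30 by the hypergeometric distribution.

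| p | SD of difference in shares | P(arms differ by 6 or more) |
|---|---|---|
| 20% | 0.104 | 0.10 |
| 30% or 70% | 0.119 | 0.16 |
| 50% | 0.130 | 0.20 |

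A difference of 6 is 6/30 = 0.20. Times a gap of 12, 15 or 18, it moves the change contrast by 2.4, 3.0 or 3.6 points.

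**4. Variance of change.** Assume a within-status SD of change of 8 (variance 64) and that all off-drug entrants resume. Then Var(change) = 64 + p(1 − p) × gap².

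| p | gap 12 | gap 15 | gap 18 | ratio to 64 |
|---|---|---|---|---|
| 20% | 87.0 | 100.0 | 115.8 | 1.36 to 1.81 |
| 50% | 100.0 | 120.25 | 145.0 | 1.56 to 2.27 |

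With 25 per arm, SE = √(2 × variance/25): 2.26 at variance 64, 2.64 to 3.04 at p = 20%, and 2.83 to 3.41 at p = 50%. If only 10% enter off drug and the gap is 15, the ratio is (64 + 0.09 × 225)/64 = 1.32. At 5% it is (64 + 0.0475 × 225)/64 = 1.17.

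**5. What adjustment recovers (p = 50%, gap 15, within-status correlation 0.5, equal variances).** The within-status score variance is then also 64 and the covariance between visits is 32.
- No adjustment: 120.25.
- Status and status by time only: 64.
- Baseline total as covariate only: 64 − 32²/120.25 = 55.5.
- Status and baseline score together: 64 × (1 − 0.25) = 48.

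The baseline total removes (120.25 − 55.5)/(120.25 − 48) = 90% of the excess and leaves residual variance 55.5/48 = 1.16 times that with status also in the model.

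**6. Which contrast, and what stratification does.** A simulation used 30 per arm, no true effect, symptom SD 7, correlation 0.5, half off drug and all resuming. Results are for gaps of 12, 15 and 18.
- SD of the unadjusted change contrast, no stratification on status: 2.42, 2.73, 2.97.
- The same contrast adjusted for status: about 1.8, as with no gap.
- Stratified on status but no model term: true SD about 1.8, while the reported SE stays at 2.39, 2.66, 2.97.
- Raw Week 2 difference: about 1.8 throughout.

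**The case against.** The strongest reply is that the protocol already provides for this. Section 2.7.1 says that baseline data including the current regimen will be used for confounder adjustment, and the detail could sit in an analysis plan that is not shown. This stands in part: it would be wrong to infer that baseline metformin information serves imputation alone. But section 2.10 does fix the model's terms, and status is not among them, so the two sections need to be brought together.

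A reader might also infer that imbalance in status biases the trial result. It does not: chance imbalance under randomisation is random error. Nor does it shift every comparison. The protocol names no primary contrast, and the raw Week 2 or Week 4 difference is untouched by this route if everyone has resumed. The protocol does allow metformin to be withheld or stopped (sections 2.6.1 and 2.8.2), so items 1 to 5 may be non-zero at follow-up in some people.

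The baseline total as a covariate would recover about 90% of the excess variance, and on the assumptions above it does better than the status terms alone (55.5 against 64). That is correct, but the stated model does not carry the baseline score as a covariate either.

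The off-drug share is unknown, and 50% is the least favourable value. If nearly all entrants share one status, little is lost. Finally, this is a pilot with no formal efficacy test planned. That limits the consequences to the estimates, which are nevertheless the pilot's purpose.

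**Conclusion.** The point holds as a gap in the stated model. Entry status can separate participants by 12 to 18 points at baseline, this gap closes by scoring rule on resumption, and no term in section 2.10 represents it. The result is extra random error in the change-from-baseline contrast and a larger SD of change and of the baseline score. The variance of change rises about 1.4 to 1.8 times at 20% off drug and 1.6 to 2.3 times at 50%. These sizes rest on an assumed within-status SD of change of 8, on resumption by all off-drug entrants, and on an off-drug share that the protocol does not give.

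Three stronger readings are not supported. The choice of age and gender as strata is not an error: stratifying on status without a model term would leave the reported SE unchanged. The SD at Weeks 2 and 4 is not inflated by this route when everyone has resumed, and section 2.4 does not say at which visit the SD is wanted. The gap of 12 to 18 does not follow from the scoring table alone; the lower end needs the dose cap of criterion (1).

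**What to change.** In section 2.10, add baseline metformin status (taking or not taking) and status by time as fixed effects in the mixed model for the primary score, and cross-refer to section 2.7.1 so that the two sections agree. Report the pilot SD within status as well as overall, so that the definitive trial can be sized for its own recruitment mix.

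Adjusting for the baseline total is a reasonable alternative that recovers most of the loss. On the assumptions above, status and baseline score together give the smallest residual variance. Stratifying on status is optional and is not sufficient without the model term.

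The cost is a line of text and a few degrees of freedom: one for status and, with three visits, two for status by time. No new data are needed, because item 1 of Table 2 already records status at baseline.
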